### Plans to promote participant retention and complete follow‐up

5.2

The study investigators will provide a careful explanation of the importance of follow‐up visits before a prospective participant gives informed consent. Participants will be asked to follow up in person and reminded of upcoming visits approximately a week in advance. Participants will also be given access to a study phone number and allowed to attend their visit ±7 days of the scheduled date to accommodate personal, work, and/or public transit schedules and further promote retention.

## STATISTICAL METHODS

6

We choose a randomized two‐arm design with an equal sample size in the arm with the provision of conditional cash and the arm with the provision of free medication. Our sample size calculation is based on Hypothesis 1a.

To investigate Hypothesis 1a, we will first test the null hypothesis that the retention rate of the group with the provision of conditional cash is less than or equal to 90% using a non‐inferiority one‐sample proportion test. We will then test the null hypothesis that the provision of conditional cash will lead to a retention rate no less than the retention rate of free medication (controlling for medication type) using a noninferiority two‐sample proportion test. Since there are two hypotheses, in the sample calculation, we applied the Bonferroni correction to ensure a familywise error rate of 0.05.^27^ Given the existing studies and preliminary results, we expect that the retention rate of the group with the provision of conditional cash will have a retention rate higher than 90%. This reflects financial incentive clinical trials in other diseases where the intervention improves retention in care, particularly studied in HIV/AIDS.^28^, ^29^

Assuming it is 90%, to ensure a statistical power of 80%, with a noninferiority margin of 8.5%, the sample size of the arm with the conditional cash required is 98.^30^ We will then test the null hypothesis that the provision of conditional cash will lead to a retention rate no less than the retention rate of free ASMs using a noninferior two‐sample proportion test. Assuming the conditional cash group has 90% of PWE who will return at 12 months, with a noninferiority margin of 12%, to ensure statistical power of 80%, the sample size of the arm with the conditional cash required is 99.

For Hypothesis 1b, we will use a one‐sample proportion test to test the null hypothesis that the percentage of PWE regularly taking ASMs at 12 months in the conditional cash arm is less than or equal to 85%, and we will use a two‐sample proportion test for the null hypothesis that the percentage of PWE regularly taking ASMs in the conditional cash arm is less than or equal to the percentage of PWE regularly taking ASMs in the free medication arm. For Hypothesis 1c, we will use a one‐sample proportion test to test the null hypothesis that the percentage of PWE with seizure freedom at 12 months in the conditional cash arm is less than or equal to 65%, and we will use a two‐sample proportion test for the null hypothesis that the percentage of seizure freedom in the conditional cash arm is less than or equal to the percentage of seizure freedom in the free medication arm.

To leverage the longitudinal observations collected during follow‐up visits at 90, 180, 270, and 360 days, we will use a generalized linear mixed effects model which allows us to study the association between multiple baseline variables (e.g., including the intervention options, education level, medication status, ASM type, distance to the study clinics) while accounting for the correlation between longitudinal observations.

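### The one-sample retention test is written against 90% but sized against 81.5%, and 98 to 100 participants give about 60% power against 81.5%, not 80%

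*Protocol article*

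**What the plan says.** Section 6 (Statistical Methods) of the protocol article rests the sample size on Hypothesis 1a, retention in care. It plans two tests for that hypothesis.

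- **One-sample test.** The null is that "the retention rate of the group with the provision of conditional cash is less than or equal to 90" percent. The same sentence calls the procedure a non-inferiority one-sample proportion test.
- **Two-sample test.** This is a non-inferiority comparison of conditional cash with free medication.

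On alpha, the section says "we applied the Bonferroni correction to ensure a familywise error rate of 0.05", because there are two hypotheses.

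The one-sample calculation reads "Assuming it is 90%, to ensure a statistical power of 80%, with a noninferiority margin of 8.5" percent, and the number required in the cash arm is 98. For the two-sample test the section says "with a noninferiority margin of 12%, to ensure statistical power of 80%, the sample size of the arm with the conditional cash required is 99". Section 1.1 (Trial design) randomizes 200 people 1:1, so the cash arm has 100.

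The section also says that retention in the cash arm is expected to be above 90%, but it plans at 90%. The value 81.5% appears nowhere in the article.

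**The concern.** There are two linked problems.

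1. **The null and the sizing disagree.** The null is written at 90% and the assumed truth is also 90%. When the truth lies on the boundary of the null, the chance of rejection is at most alpha, so 80% power is impossible for that pair. The calculation must have used another null, and the margin points to 90% minus 8.5 points, which is 81.5%. An analyst who follows the null sentence and one who follows the sample-size sentence could reach opposite verdicts on the same data. With 92 of 100 retained, for example, an exact test at one-sided 0.025 rejects 81.5% (it needs 90) but not 90% (it needs 96).

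2. **The stated power looks too high even against 81.5%.** The shortcut formula that gives 98 uses the variance at the alternative for both error terms. Here the null variance is about two-thirds larger, so the critical value behind the formula is too lenient.

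The stakes are the verdict on the hypothesis that sizes the trial, the power reported for it, and the wording of a success. Rejecting 81.5% does not show that the 90% retention target was met.

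**Working it through.** **Inputs (protocol article, section 6, unless noted).** True retention 0.90. Margin 0.085. Power 80%, so z = 0.8416. Familywise alpha 0.05 split over two hypotheses, so 0.025 each, z = 1.96. Cash arm 98 as calculated, 100 as randomized (section 1.1). One-sidedness is inferred from the form of the null and supported by steps 1 and 2.

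**1. Reproducing 98.** With the variance at 90% in both terms and a null of 0.90 − 0.085 = 0.815:

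n = 0.90 × 0.10 × (1.96 + 0.8416)² / 0.085² = 97.8, rounded up to 98.

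One-sided 0.05 would give 78 and one-sided 0.0125 would give 119, so 0.025 is the level used.

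**2. Cross-check on the two-sample figure.** n = 2 × 0.09 × (1.96 + 0.8416)² / 0.12² = 98.1, rounded up to 99, as stated. The alpha is confirmed and this figure stands.

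**3. The null as literally written.** Null 0.90, truth 0.90: power cannot exceed 0.025. At n = 100 an exact test needs at least 96 retained, and P(X ≥ 96 | 0.90) = 2.4%. This shows only that the two sentences are incompatible.

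**4. The variance.** At the null: 0.815 × 0.185 = 0.151. At 90%: 0.090. With the null variance in the critical-value term (score formula):

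n = [(1.96 × √0.1508 + 0.8416 × 0.3) / 0.085]² = [(0.7611 + 0.2525) / 0.085]² = 142.2, so 143.

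The exact test first reaches 80% at n = 136 and stays there from n = 149.

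**5. Power of tests that hold one-sided 0.025, null 81.5%, truth 90%.** The exact and score tests have the same cut-offs here.

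| n | Reject at | Type I error | Power |
|---|---|---|---|
| 98 | ≥ 88 | 1.8% | 61.0% |
| 99 | ≥ 89 | 1.7% | 59.6% |
| 100 | ≥ 90 | 1.5% | 58.3% |

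**6. Wald test (estimated variance), same setting.**

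| n | Reject at | Type I error | Power |
|---|---|---|---|
| 98 | ≥ 87 | 3.7% | 72.7% |
| 100 | ≥ 88 | 5.6% | 80.2% |

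**7. Sensitivity to the true rate (exact test, null 81.5%).**

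| True retention | n = 98 | n = 100 |
|---|---|---|
| 90% | 61% | 58% |
| 91% | 73% | 71% |
| 92% | 84% | 82% |
| 93% | 92% | 91% |

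**8. Sensitivity to alpha.** At one-sided 0.05, without the Bonferroni split, exact power at a true 90% is 73% at n = 98 and 70% at n = 100, still short of 80%.

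**The case against.** **The section names a non-inferiority test and gives a margin, so 81.5% is implied.** This is the best reply, and much of it stands. The null sentence names the reference rate and leaves out the margin. A reader might infer from it that the test is almost certain to fail when retention is 90%. The documents do not support that, because the 2.4% in step 3 belongs to a superiority test against 90% that the section does not plan. The written null is still wrong, since 81.5% is never stated.

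**The arithmetic is correct under its own formula, and the choice of test can be left to the analysis plan.** Both are true. But the article itself states 80% power. The Wald rule comes near that only by exceeding the allotted 2.5%, and the exact and score tests, which hold it, give about 60%.

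**Planning at 90% is conservative.** The section does expect more than 90%, and at a true 92% the power is 82 to 84%. The stated 80% is nevertheless tied to a true rate of 90%.

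**Two further readings go too far.** The order of the two tests might suggest that the one-sample test is a gate for the comparison with free medication. Alpha is split by Bonferroni and nothing makes the second test depend on the first. Nor does a low chance that both tests succeed contradict the plan, which claims 80% for each test and nothing for the pair.

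**Conclusion.** The point holds on both counts.

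- **Null.** The one-sample null for Hypothesis 1a is written as 90% or less, whereas the planned margin and the 98 participants correspond to 81.5% or less. The two sentences must be reconciled.
- **Power.** Against 81.5%, at a true 90% and one-sided 0.025, power is 58 to 61% with 98 to 100 participants, about 20 points below the stated 80%. By the score formula, 80% needs 143 in the cash arm.

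This rests on one-sided 0.025 per test, which is the level that reproduces both stated sample sizes, on a test that holds that level, and on all randomized cash-arm participants being analysed. If true retention is 92%, the shortfall disappears. The randomized comparison with free medication and its 99 per arm are not affected.

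**What to change.** In section 6:

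1. State the one-sample null as cash-arm retention of 81.5% or less, and show it as 90% minus the 8.5-point margin.
2. Name a test that holds one-sided 0.025, either exact binomial or score.
3. Replace the 80% power claim with about 60% at a true rate of 90% for 98 to 100 participants, and add 82 to 84% at a true rate of 92%, since retention above 90% is expected.
4. Word a success as retention above 81.5%, not as meeting the 90% target.

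The cost is a few sentences and a less favourable stated power, with no extra participants. Keeping 80% power at a true 90% would instead need about 143 in the cash arm. Lowering the benchmark until 100 participants reach 80% is not a substitute: it would fit the margin to the sample, and the resulting power would hinge on the discreteness of the binomial.

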### Eligibility criteria

2.2

PWE will be screened in person and enrolled on a “first come, first served” basis. The goal is to enroll a person with active epilepsy. The person will have therefore experienced two or more recurrent, unprovoked seizures in the past year (inclusion criterion) and not have had any other diagnosis that can better explain the symptoms, as evaluated by the study neurologists (one Guinean and one U.S.). Specifically, patients with exclusively febrile seizures, pseudo‐seizures, and other movement disorders or episodic events that are not primary epilepsy are not eligible. The study will include a brain MRI such that secondary seizures from a space‐occupying lesion (secondary to tumor, stroke) can be detected and referred to usual care but not enrolled. Similarly, seizures that are provoked (e.g., alcohol withdrawal) will be queried through the intake forms and corroborated by physical examination and extant medical records.

Inclusion criteria are (1) resident of Guinea, 18 years or older, presenting to one of the study sites in Guinea; (2) able to provide informed consent or have a next of kin proxy provide informed consent when appropriate; (3) experienced two or more recurrent, unprovoked seizures in the past year; (4) able to provide a clinical history or have a next of kin provide it; (5) not taking a daily ASM for epilepsy for the past 30 days or more for any reason; (6) willing to have his/her data sent anonymously to the U.S. study site; and (7) anticipated to be able to return for follow‐up visits for 360 days.

Exclusion criteria are (1) any other diagnosis that can better explain the symptoms, making the diagnosis of primary, active epilepsy unlikely; (2) unable to undergo the study procedures; (3) age less than 18 years old due to the need to measure several self‐reported outcomes; (4) unable to provide informed consent (or have an appropriate proxy informed consent); (5) currently pregnant or lactating; (6) secondary seizures, for example, due to a condition that requires imminent treatment (e.g., malignancy, alcohol withdrawal); (7) critically ill; (8) exclusively pseudo‐seizures/nonepileptic behavioral events; (9) unwilling to take an ASMs for epilepsy; (10) already treated with ASMs for other purposes (e.g., mood, pain); (11) known to be unable to return for follow‐up visits.

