### Intervention description

3.2

The education intervention will be given to each participant upon study enrollment in the form of a prerecorded, standardized video, made by the investigators, lasting approximately 30 min. The video is designed for people with low literacy and will answer the following basic questions: [What is a seizure? What is epilepsy? Why does epilepsy occur? Why is epilepsy a brain disorder? What works to treat epilepsy? What does not work to treat epilepsy? Why are ASMs important?] The video will be available in local languages (Sousou and Malinké), English, and French and shown on electronic tablets. A question‐and‐answer period, led by the study neurologists, will follow with no limitations on the amount of time. A flyer providing basic, written information on the education intervention will be given.

ASMs will be provided free of charge and prescribed for the participants in the study arm that includes the medication intervention. The ASM choice will be determined at the discretion of the neurologist in the context of the patient's history. There is no one best ASM for all patients, and most ASMs provide similar efficacy but dissimilar side effects and safety. There will be a total of seven possible ASMs to be used.

CCT will be conditioned on the return for follow‐up visits to the outpatient epilepsy clinic for scheduled appointments (±7 days every 90 days). Each visit for those in the CCT groups will entail the provision of 15 USD (given in the equivalent of Guinean Francs) to participants. This amount is anticipated to be a “nudge” (i.e., mildly incentivizing) as it exceeds the general cost of transportation for a return visit in the area (~5 USD on average) and ASM (which approximately costs ~4–10 USD for a monthly dosage in Guinea).^11^ It is important to note that this nudge will ensure participants in the CCT arm can afford the ASM, which enables study staff to assess outcomes from behavioral change rather than affordability considerations. The transfer will also be conditional on presence at visits, not on seizure outcomes. This ensures that participants are not penalized for aspects of their illness that are beyond their control.

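### The Hypothesis 1a arm comparison is stated both with and without adjustment for medication type, and adjusting for the ASM used in the study can bias the randomised effect

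*Protocol article*

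**What the plan says.** All references are to the protocol article.

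- **Section 6, Hypothesis 1a.** The two-arm test asks whether retention with conditional cash is "no less than the retention rate of free medication (controlling for medication type) using a noninferiority" two-sample proportion test. The next paragraph gives the same test as "no less than the retention rate of free ASMs using a noninferior" two-sample proportion test. It names no covariate there and derives 99 for the cash arm.
- **Section 6, longitudinal analysis.** A generalized linear mixed model will "study the association between multiple baseline variables" and outcome, with examples "including the intervention options, education level, medication status, ASM type, distance to the study clinics".
- **Section 2.2, inclusion criterion 5.** Every participant is "not taking a daily ASM for epilepsy for the past 30 days or more for any reason".
- **Sections 3.1 and 3.2.** "The ASM choice will be determined at the discretion of the neurologist", and "There will be a total of seven possible ASMs to be used". In one arm the drug is prescribed and supplied free. In the other, people already randomised to cash receive a recommendation and advice on buying.
- **Section 4.1.** Participants and the site staff who deliver the intervention are described as blinded to the hypothesis. Blinding to arm is not described.

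Neither medication type nor medication status is defined, and no section gives the order of ASM choice and allocation.

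**The concern.** The total effect of allocation on retention is what randomisation protects. A covariate fixed before randomisation leaves that effect intact. A covariate that can itself be a result of allocation does not: conditioning on it removes any part of the effect that runs through it. It can also open a spurious association between arm and prognosis.

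The ASM used in the study looks like a covariate of the second kind. Nobody is on a daily ASM at entry, and the text describes the drug by reference to the assigned arm. The protocol's own prices give a reason for the arms to differ. Section 3.2 puts an ASM at about 4 to 10 USD a month and transport at about 5 USD a visit. Three months of drug plus one trip therefore cost 3 × 4 + 5 = 17 to 3 × 10 + 5 = 35 USD, against 15 USD of cash per visit. Price could affect which drug is recommended or bought in the cash arm, but not in the free arm.

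In a noninferiority test, a shift that favours cash raises the chance of a false claim. Separately, the text does not fix which of two analyses is the Hypothesis 1a test.

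**Working it through.** **1. Reproduce the stated sample sizes.** Inputs from section 6: retention 90%, power 80%, margins of 12 points (two-sample) and 8.5 points (one-sample), and familywise error 0.05 over two tests, hence 0.025 each. Assumed: 90% in the free arm as well, and one-sided testing (inferred from the match). With z = 1.960 and 0.842, (1.960 + 0.842)² = 7.849.

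- Two-sample: (0.9×0.1 + 0.9×0.1) × 7.849 / 0.12² = 98.11, rounded up to 99. The protocol says 99.
- One-sample: 0.9×0.1 × 7.849 / 0.085² = 97.77, rounded up to 98. The protocol says 98.
- At one-sided 0.05 both would be 78; at 0.0125 both would be 119.

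The matching formula has no covariate term, so the stated size belongs to the unadjusted test.

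**2. How far adjustment could move the arm difference (assumed values).** Suppose one ASM type lowers retention by d, and the share of participants on it is higher in the cash arm by Δq. The adjusted difference then departs from the total arm effect by d × Δq:

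| Δq | d | Gap |
|---|---|---|
| 0 | any | 0 |
| 0.10 | 0.10 | 1 point |
| 0.20 | 0.15 | 3 points |
| 0.40 | 0.20 | 8 points |

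If the type is commoner in the free arm, the sign reverses.

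**3. A gap is possible even if ASM type has no effect on retention (assumed values).** Let half of the participants have a prognostic factor, with retention 95% without it and 85% with it, and let the true arm effect be 0. In the free arm, 20% take type A whatever the factor. In the cash arm, 30% take it without the factor and 90% with it.

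- Cash, type A: (0.15×0.95 + 0.45×0.85)/0.60 = 87.5%, against 90% in the free arm: −2.5 points.
- Cash, other type: (0.35×0.95 + 0.05×0.85)/0.40 = 93.75%, against 90%: +3.75 points.
- Weights from the arm shares (product over sum): 0.2×0.6/0.8 = 0.150 and 0.8×0.4/1.2 = 0.267.
- Adjusted difference: (−2.5×0.150 + 3.75×0.267)/0.417 = +1.5 points, where the truth is 0.

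If the same choice rule applies in both arms (20% without the factor and 60% with it), the adjusted difference is 0.

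**4. Effect on the error rate.** Take 100 per arm and true retention of 90% (free) against 78% (cash), exactly at the margin. SE = √(0.9×0.1/100 + 0.78×0.22/100) = 0.0511. With a shift b in favour of cash, the one-sided error is 1 − Φ(1.960 − b/SE):

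| Shift b | One-sided error |
|---|---|
| 0 | 2.5% |
| 1 point | 3.9% |
| 2 points | 5.8% |
| 3 points | 8.5% |
| 4 points | 11.9% |

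**The case against.** **The timing is inferred.** No section says that the ASM is chosen after allocation, and section 6 calls these variables baseline. Medication type might mean the drug that the neurologist recommends or prescribes. That would exist in both arms and could follow one rule based on history, in which case there is no bias. This stands, and it limits the claim to *can bias*. It does not remove the point, because section 3.1 speaks of a recommendation to people already randomised, and nothing says that an intended ASM is recorded beforehand.

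**The variables may be history.** Criterion 5 excludes recent daily use, not past use. Table 1 reports previous ASM use and the drugs ever taken in a cohort expected to resemble the trial's participants. Read that way, medication status varies between participants and is a sound baseline covariate. This stands. A reader might infer that medication status must be constant or post-randomisation, but the text does not settle it.

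**The mixed model is not the Hypothesis 1a test.** It is described as an association analysis with an illustrative covariate list. This stands, so it is a secondary matter.

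**A proportion test takes no covariate, so the named test is already unadjusted.** Stratified noninferiority tests exist, and the parenthesis may intend one. The text thus supports two different analyses, which is the reason to change it.

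**Conclusion.** The Hypothesis 1a arm comparison is not uniquely defined. It is stated once with adjustment for medication type and once without, and it is sized without. If the adjustment uses the ASM prescribed, recommended or taken during the study, it does not target the total randomised effect on retention and can bias it.

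The size is unknown. On assumed inputs the gap runs from 0 to 8 points. A shift of 0 to 4 points in favour of cash, at the 12-point margin with 100 per arm, would take the one-sided error from 2.5% to about 12%. The gap is 0 if ASM choice does not depend on arm.

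A reader might go further and infer that the adjustment certainly hides a cash-arm deficit caused by participants who buy no ASM, and so pushes the result toward noninferiority. The documents do not support this. They do not say that taking no ASM counts as a medication type, they give no purchase or retention rates by type, and the cash is paid for attendance whether or not a drug is bought. Neither direction nor size can be claimed.

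**What to change.** - Delete the medication-type parenthesis in section 6, so that the main Hypothesis 1a comparison is unadjusted. If adjustment is wanted, use only pre-randomisation variables such as site, distance to clinic and education, and name the stratified or model-based method.
- In the mixed model, keep on-study ASM type and on-study medication status out of any model used to estimate the arm effect, or label such models exploratory. Prior ASM history recorded at baseline may stay. Define both terms.
- Report ASM type by arm descriptively.

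The cost is wording in the protocol, and in the SAP if it repeats the phrase. The sample size stays at 99 (two-sample) and 98 (one-sample), because both are already unadjusted calculations.

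### Analysing the two Hypothesis 1a tests by Holm's procedure instead of Bonferroni would gain some power at the same familywise error of 0.05 and the same 200 patients

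*Protocol article*

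**What the plan says.** The Statistical Methods section of the protocol article bases the sample size on Hypothesis 1a and describes two tests.

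- **One-sample test.** It addresses the "null hypothesis that the retention rate of the group with the provision of conditional cash is less than or equal to 90"%. The size statement is: "margin of 8.5%, the sample size of the arm with the conditional cash required is 98".
- **Two-sample test.** Conditional cash is compared with free medication, "with a noninferiority margin of 12%, to ensure statistical power of 80"%. The required cash arm is 99.

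On multiplicity the text says "we applied the Bonferroni correction to ensure a familywise error rate of 0.05". The same sentence opens by tying this to sizing: "Since there are two hypotheses, in the sample calculation, we applied the Bonferroni correction". That sentence concerns the sample size calculation. The article gives no per-test significance level for the final analysis and no rule making the second test depend on the first. It does not say that both tests must succeed, and it names no alternative to Bonferroni.

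**The concern.** With two tests and a familywise rate of 0.05, Bonferroni holds each test at 0.025 whatever the other one shows. Once one null has been rejected at 0.025, keeping the remaining test at 0.025 adds nothing to the promised guarantee. Holm's procedure uses this: the smaller p-value must be at or below 0.025, and the other is then tested at 0.05. It is valid under any dependence between the tests, which matters because both use the cash arm. It needs no pre-set order.

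If Bonferroni were also the analysis rule, the trial could miss one of the two retention conclusions when the data would support it at the error rate the plan already accepts.

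**Working it through.** **Inputs from the protocol article.** Assumed cash retention is 90% (Statistical Methods). Free-medication retention is also taken as 90%, since the Objectives section hypothesises similar retention at that level. Margins are 8.5 and 12 points, and power is 80% per test. The trial randomises 200 patients 1:1 (Trial design), so 100 per arm. Sidedness is not stated as a number; I take both tests as one-sided, with the first judged against 90 − 8.5 = 81.5%.

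**Reproducing the stated sizes.** With z(0.975) + z(0.80) = 1.960 + 0.842 = 2.802, squared 7.849:

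- One-sample: n = 0.9 × 0.1 × 7.849 / 0.085² = 97.77, so 98.
- Two-sample: n = 2 × 0.9 × 0.1 × 7.849 / 0.12² = 98.11, so 99 per arm.

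Both match. One-sided 0.05 per test would give 78 and 78, and one-sided 0.0125 would give 119 and 119. The plan's figures therefore fit 0.05/2 = 0.025 per test.

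**Normal approximation, 100 per arm.** The standardised effects are 0.085/√(0.09/100) = 2.833 and 0.12/√(0.18/100) = 2.828. The two statistics share the cash arm, so their correlation is 1/√2 = 0.707. Let S(a, b) be the probability that test 1 passes its critical value at level a and test 2 at level b. Then:

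- Bonferroni, both succeed: S(0.025, 0.025).
- Holm, both succeed: S(0.05, 0.025) + S(0.025, 0.05) − S(0.025, 0.025).
- At least one succeeds, either procedure: 80.9% + 80.7% − 72.4% = 89.2%.

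**Full enumeration of two Binomial(100, 0.9) arms.** I did this once with Wald tests, and once with an exact binomial one-sample test and a Farrington-Manning two-sample test.

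| Method, 100 per arm | Procedure | One-sample | Two-sample | Both | At least one |
|---|---|---|---|---|---|
| Normal approximation | Bonferroni | 80.9% | 80.7% | 72.4% | 89.2% |
| | Holm | 85.2% | 85.1% | 81.1% | 89.2% |
| Wald, enumerated | Bonferroni | 80.2% | 81.3% | 74.7% | 86.7% |
| | Holm | 80.2% | 84.8% | 78.2% | 86.7% |
| Exact / Farrington-Manning | Bonferroni | 58.3% | 78.0% | 56.4% | 80.0% |
| | Holm | 67.8% | 79.6% | 67.4% | 80.0% |

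The Wald one-sample test gains nothing at n = 100 because its success cut-off is 88 of 100 at both 0.025 and 0.05. The exact test's cut-off moves from 90 to 89. One patient fewer per arm changes the Wald picture: at n = 99, both succeed 68.0% of the time under Bonferroni and 76.9% under Holm.

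**Familywise error.**

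- *Normal model.* Holm's rate is 0.0375 with both nulls at their boundary. It is 0.0496 with only the first null true (81.5% in both arms).
- *Exact and Farrington-Manning tests.* For (cash, free medication) retention of (78%, 90%), (81.5%, 93.5%), (81.5%, 90%) and (86%, 98%), Holm's rate is 0.025, 0.030, 0.027 and 0.046.
- *Wald tests.* These do not hold their level. With both nulls at their boundary (81.5%, 93.5%), the familywise error is 0.063 even under Bonferroni. At (87%, 99%), where only the second null is true, the error is 0.047 under Bonferroni and 0.076 under Holm.

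**The case against.** **The correction is tied to sizing only.** This is true. Sizing by Bonferroni is compatible with analysing by Holm, and an analysis plan not shown here may do so. A reader might infer that the article commits the final analysis to 0.025 per test; it does not say that. What stands is that Bonferroni is the only multiplicity procedure the article names, so stating the analysis rule would settle the matter.

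**Nothing is wrong with Bonferroni.** Also true. It controls the stated rate, and 98 and 99 reproduce. A reader might infer from joint success rates of 56% to 75% that the trial misses its power target. The target is 80% for each test separately, and the plan's own approximation meets it; no joint target is set. Nor should the 58% one-sample power be blamed on Bonferroni. At the same 0.025 it falls from 80.2% to 58.3% because the test changes from Wald to exact.

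**The gain depends on the test.** It does, and the article names no test statistic beyond one-sample and two-sample proportion tests. The stated sizes use the unpooled variance. The matching Wald tests at the planned 100 per arm show the smallest gain, 3.5 points.

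**If both tests had to succeed, no alpha split would be needed.** Correct: each could then be run at one-sided 0.05, giving 69.2% for both with exact and Farrington-Manning tests, against Holm's 67.4%. It is tempting to read Hypothesis 1a that way, but the article declares familywise control and not a both-must-succeed rule. Holm works within what is declared.

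**Holm costs something in reporting.** Bonferroni gives simple simultaneous one-sided 97.5% bounds, and matching bounds for Holm are less simple. That is a real but small cost.

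**Conclusion.** The point holds as a minor efficiency gain. At the familywise rate already stated, Holm would raise the chance that both Hypothesis 1a tests succeed by about 3.5 to 11 points at 100 per arm, depending on the test statistic. It would not change the chance of at least one success. These figures assume 90% retention in both arms, all 200 patients analysed, one-sided tests and the stated margins. The error guarantee carries over only if the individual tests hold their level, which the Wald versions do not. The documents do not support calling the Bonferroni choice or the sample size an error.

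**What to change.** In the Statistical Methods section, keep the Bonferroni-based sample size and add one sentence: the two Hypothesis 1a tests will be analysed by Holm's step-down procedure at a familywise one-sided error of 0.05, with the smaller p-value required to be at or below 0.025 and the other then tested at 0.05. Name tests that hold their level, such as an exact one-sample test and a Farrington-Manning two-sample test, and settle this before outcome data are examined.

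The step to Holm needs no extra patients or data, and no conclusion available under Bonferroni with the same tests is lost. Two costs should be acknowledged. Confidence bounds that match Holm are less simple to report. Separately, if Wald tests were intended, moving to an exact one-sample test lowers that test's power whichever multiplicity procedure is used; Holm recovers part of the loss (58.3% to 67.8%).
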